## Abstract

Inactivity and an unhealthy diet amongst others have led to an increased prevalence of overweight and obesity even in young children. Since most health behaviours develop during childhood health promotion has to start early. The setting kindergarten has been shown as ideal for such interventions. “Join the Healthy Boat” is a kindergarten-based health promotion programme with a cluster-randomised study focussing on increased physical activity, reduced screen media use, and sugar-sweetened beverages, as well as a higher fruit and vegetable intake. Intervention and materials were developed using Bartholomew's Intervention Mapping approach considering Bandura's social-cognitive theory and Bronfenbrenner's ecological framework for human development. The programme is distributed using a train-the-trainer approach and currently implemented in 618 kindergartens. The effectiveness of this one-year intervention with an intervention and a control group will be examined in 62 kindergartens using standardised protocols, materials, and tools for outcome and process evaluation. A sample of 1021 children and their parents provided consent and participated in the intervention. Results of this study are awaited to give a better understanding of health behaviours in early childhood and to identify strategies for effective health promotion. The current paper describes development and design of the intervention and its implementation and planned evaluation.* Trial Registration*. The study is registered at the German Clinical Trials Register (DRKS), Freiburg University, Germany, ID: DRKS00010089.

## 1. Introduction

Although some countries report a plateau of childhood obesity, the prevalence of overweight and obesity has risen continuously during the last decades and plateaued at an unhealthy high level [1]. Main reasons for this development are a diet high in calories [2, 3] in combination with an inactive lifestyle [4] which is often already established at a young age. These behaviours have not only been linked to an increased body weight but also to chronic diseases such as cardiovascular diseases and Type 2 diabetes [5].

Therefore, interventions to promote a healthy lifestyle must start early. Risk factors are already present in young children [6] and most health behaviours develop at an early age [7], which are then carried forward into youth and adulthood [8].

There are many health promoting interventions for children—some more successful than others. Effective and sustainable health promotion programmes are multicomponent and include physical activity as well as nutrition components and are tailored to a specific target group but also include the whole environment around that group [9, 10]. For children, not only family but also important bases of socialisation such as kindergartens should be involved in health promoting interventions. There they can be reached together with their peers, independent of their background and for a longer period of time. Therefore, kindergartens are promising settings to intervene and for children to learn health behaviours, also because of the ability to stay in close contact with their parents [11].

Intervention planning for health promotion programmes should be scientifically sound and based on a theoretical model [12]. The complex process of an intervention development and its implementation and evaluation should always be guided by a planning model [13]. However, intervention planning of health promotion programmes is rarely targeted scientifically and only few developments of interventions and their contents are described in more detail [12, 14].

Based on experiences and results of the sister project “Join the Healthy Boat” in primary schools [15–17], the intervention was designed and implemented in kindergartens in the state of Baden-Württemberg, southwest Germany.

The aim of this paper is to address the development of the health promotion programme “Join the Healthy Boat – Kindergarten,” its implementation and planned evaluation including sample and methods. Development steps are shown in detail as well as the particular intervention contents and their implementation.

## 2. Materials and Methods

### 2.1. Programme Development and Implementation

“Join the Healthy Boat” is a multicomponent health promotion programme for kindergarten children (three to six years old) in southwest Germany, which was developed by means of Bartholomew's Intervention Mapping Approach (IMA; see Figure 1) [18].

The IMA offers guidance for a theory-based development of interventions for health promotion and includes six detailed steps: (1) needs assessment; (2) identification of intervention targets; (3) selection of theory-based intervention methods and applications; (4) integration of methods and applications into an organised programme; (5) plan for adoption, implementation, and sustainability; and (6) an evaluation plan [18].

### 2.2. Needs Assessment

During the first step “needs assessment,” literature was systematically reviewed for the topics “physical activity and leisure time activities” and “diet and nutrition” as well as for kindergarten and school-based health promotion interventions. In addition, weekly meetings of an interdisciplinary scientific team were held as well as regular focus groups with kindergarten staff and parents. For “Join the Healthy Boat,” four key topics evolved out of the needs assessment: “promotion of (everyday) physical activity,” “reduction of screen media use,” “decrease of sugar-sweetened beverages,” and “increase of fruit and vegetable intake.” These key topics were oriented towards the children's needs, specific to the target group and well implementable in a kindergarten-based health promotion programme.

### 2.3. Intervention Targets

These main topics, which were compiled during the needs assessment, were concretised and defined more thoroughly in the second step “identification of intervention targets.” With the use of so-called matrixes (extensive table templates), which are prestructured by IMA, behaviours and programme targets were developed and specified and resulted in children having to receive new knowledge and opportunities to try out new, alternative behaviours (e.g., activity games, different foods). For nutrition-specific topics, direct offers of healthy food played an important role.

### 2.4. Theory-Based Strategies

Subsequently, during step three, methods and practical strategies to attain behaviour changes were chosen, which suit target group and intervention aims (defined in step two) best. For the health promotion programme “Join the Healthy Boat,” the social-cognitive theory (SCT) by Bandura [19] and Bronfenbrenner's ecological framework for human development [20] were chosen.

The SCT assumes that behaviours are determined by personal and environmental factors as well as behaviours. Bronfenbrenner on the other hand presumes that personal relationships and social interactions influence people's (health) behaviours [20]. Therefore, measures for behaviour as well as situation/setting change can be guided. The ecological framework for human development [20] demonstrates the importance of an involvement of family and peer group as well as situational change. Newly learnt behaviours can only be maintained if they are supported by all parts of the child's living environment. The methods used in the SCT [19], such as knowledge transfer, modelling, self-evaluation, reinforcement, promotion of self-efficacy, and setting goals [21], are most suitable to achieve health-related behaviour changes in kindergarten children.

To ensure sustainability and long-term integration into the kindergarten routine, the programme applies a teacher-centred approach, which enables the implementation of profound health promoting changes in kindergarten environments and the support of children's behaviour change continuously.

### 2.5. Intervention Design and Materials

During step four “integration of methods and applications into an organised programme,” intervention materials were designed and based on the defined programme targets and selected theoretical models from the previous steps. The materials were developed following the so-called orientation plan for kindergartens in southwest Germany [22] and in cooperation with a pedagogical advisory board consisting of kindergarten and primary school teachers as well as pedagogues. The materials are comprised of 20 exercise and games lessons as well as 30 ready-to-use ideas and action alternatives and lessons in order to get children to be more physically active and gain knowledge about their body and health as well as eat more healthily. In order to incorporate physical activity into the daily kindergarten routine, short activity games (5–7 minutes each) are part of the materials and in order to reach not only children but also their parents, materials for parents meetings and parental letters were included in three languages. During the developmental phase, intervention materials were tested for six months in 13 pilot kindergartens. An overview of the intervention's content can be found in Figure 2.

To ensure sustainability and long-term integration of “Join the Healthy Boat,” during the fifth step of IMA a train-the-trainer approach (i.e., kindergarten teachers are trained to train further kindergarten teachers) was chosen and developed [23]. For each of the 44 districts in southwest Germany, a trainer-tandem is responsible for the training courses which are held twice a year in each region. During these training courses, kindergarten teachers receive all intervention materials for free. The trainers, who are also kindergarten teachers, are trained twice a year and are intensely supported by an interdisciplinary project team at Ulm University. Apart from its cost-effectiveness [24], one advantage of this approach is that kindergarten teachers are trained by a colleague and no external expert, which enhances acceptance of the programme and enables a higher sustainability [25].

### 2.6. Study Design and Planned Evaluation

The last step of IMA guides through the planning of an evaluation of the intervention programme, which for “Join the Healthy Boat” is the so-called “Health Survey.” It was designed as a prospective, stratified, cluster-randomised longitudinal trial with an intervention and a control group and is registered at the German Clinical Trials Register (DRKS), Freiburg University, Germany, ID: DRKS00010089. The study protocol was designed in 2015 and approved by the ethics committee of Ulm University (Application Number 188/15) as well as the Ministry of Culture and Education in 2016.

Participating kindergartens were recruited from all kindergartens in southwest Germany, which have received written information about programme and study, asking interested kindergarten teachers to participate. Only kindergartens which have not previously taken part in the programme were included in the study. To ensure a similar number of children in intervention and control group, stratification of randomisation was carried out on three levels on the basis of kindergarten size, that is, kindergartens with 15 or less participating children, with 16–25 participating children, and with more than 25 participating children. Therefore, 31 kindergartens were assigned to intervention group and 31 kindergartens to control group. Children within the recruited kindergartens were eligible if they were between three and five years old at the time of baseline measurements and their parents provided a signed consent form.

### 2.7. Statistical Considerations

Further, power considerations were made prior to the study. Because of the explorative nature of this study, no adjustment for multiple testing will be made. A *p* value of less than 0.05 will be considered as significant. Subject to the number of participating kindergartens, an effect size of 0.325 (continuous outcome) can be detected with a statistical power of 0.8. The intraclass correlation coefficient was assumed as 0.05 with 40 participating children per kindergarten to reach this power. Due to the data's clustered structure, calculations will be made applying adequate statistical methods (GEE models [26]) for hierarchical data (children within kindergartens). Further details can be found in Table 1. The study's evaluation will be carried out on the basis of the intention-to-treat approach. For further assessments of effects in particular subgroups (e.g., children with migration background, overweight children) additional explorative analyses are planned. The results of all statistical tests will be interpreted in an explorative sense and not in a confirmatory way. Additionally, all main outcome variables will be adjusted for relevant socioeconomic variables (e.g., age, gender, and background).

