**Figure 3 fig3:**
[figure not shown]
Overview of recruited children, kindergartens, and kindergarten teachers, including consent for the different substudies.

**Table tab1a:** (a) Main outcomes

Outcome	Statistical analysis
Change in variables for nutrition (consumption of sugar-sweetened beverages, fruit, vegetables, high-calorie food; all variables are ordinal)	GEE model for follow-up measurement

Change in child's time spent with screen media (hours per week, ordinal/quasi-continuous variables)	GEE model for follow-up measurement

Change in child's physical activity/energy expenditure (physical activity: dichotomous, energy expenditure: continuous variables)	GEE model for follow-up measurement

Change in health knowledge and attitude of parents and kindergarten teachers (nominal/ordinal variables)	GEE model for follow-up measurement

**Table tab1b:** (b) Secondary outcomes

Outcome	Statistical analysis
Change in anthropometric parameters (waist circumference, waist-to-height ratio, BMI, subcutaneous fat; all variables are continuous)	GEE model for difference between follow-up and baseline

Change in child's quality of life (EQ5D-Y Proxy Version, KINDL parent's version; continuous variables)	GEE model for difference between follow-up and baseline

Child: change in days sick leave, doctor's consultation, hospitalisation; parents: absence from work due to children's illness (continuous variables)	GEE model for difference between follow-up and baseline

Change in child's motor skills (continuous variables)	GEE model for difference between follow-up and baseline

Environment of kindergarten and change in environment of kindergarten (continuous and categorical variables; measured on kindergarten level)	*t*-test or Wilcoxon test as appropriate, respectively, *χ*^2^-test or Fisher's exact test as appropriate for baseline and difference between follow-up and baseline

Change in laboratory parameters (saliva, cheek swab): metabolic and inflammatory parameters, for example, IL-6, TNF*α*, leptin, epigenetic investigation (continuous variables)	GEE model for difference between follow-up and baseline

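### The size stratum used in randomisation is not named in the analyses; if it is related to an outcome, standard errors are overstated and tests are conservative

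*Protocol article*

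**What the plan says.** Section 2.6 of the Protocol article states that "stratification of randomisation was carried out on three levels on the basis of kindergarten size", with cut-points at 15 or fewer, 16 to 25, and more than 25 participating children. The reason given is "To ensure a similar number of children in intervention and control group". Section 3 (Results) reports 33, 20 and 9 kindergartens in these strata, and 511 control and 510 intervention children in 31 kindergartens each.

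On analysis, section 2.7 specifies GEE models for children within kindergartens and says that "all main outcome variables will be adjusted for relevant socioeconomic variables (e.g., age, gender, and background". That sentence covers main outcomes only.

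Table 1(a) names a GEE model for the follow-up measurement for each main outcome. Most secondary outcomes in Table 1(b) get a "GEE model for difference between follow-up and baseline". The exception is the kindergarten environment, measured at kindergarten level, which gets a t-test or Wilcoxon test, or a chi-square or Fisher's exact test. Table 1 lists no covariates, and neither it nor section 2.7 mentions the size stratum.

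**The concern.** Stratified allocation makes the arms alike in the stratification factor. If that factor is related to the outcome, the treatment estimate varies less from one randomisation to the next than it would under simple allocation. An analysis that omits the factor leaves its variation in the residual and reports a standard error for a less balanced design. Intervals are then too wide, p values too large, and the true type I error falls below the nominal level.

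No false positives arise. The risk is a missed effect: section 2.7 keeps a threshold (a p "value of less than 0.05 will be considered as significant"), and the study is meant to identify strategies that work. The kindergarten-level tests are the most exposed, because no within-kindergarten variance dilutes the stratum's share.

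**Working it through.** **Inputs from the article.** 62 kindergartens, strata 33/20/9, 31 per arm, 1021 children (mean 1021/62 = 16.5), ICC 0.05.

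**Assumptions.** Two-sided alpha 0.05; continuous outcome with SD 1; cluster sizes within strata (about 1,050 children in total); 17/10/4 kindergartens in one arm and 16/10/5 in the other; and the strength of the stratum–outcome association, for which the article gives nothing.

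**1. The plan's own figure.** Section 2.7 says that "an effect size of 0.325 (continuous outcome) can be detected with a statistical power of 0.8" and that "The intraclass correlation coefficient was assumed as 0.05 with 40 participating children per kindergarten to reach this power". The design effect is 1 + 39 × 0.05 = 2.95. With 11 kindergartens per arm (440 children), 2.80 × √(2 × 2.95/440) = 0.324. The figure therefore reproduces if 22 kindergartens are assumed; the article does not give the number. Stratification plays no part in it.

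**2. Benchmark.** At the achieved size the design effect is 1 + 15.5 × 0.05 = 1.77, so the standard error is √(2 × 1.77/510.5) = 0.083. The simulation below matches this when the stratum has no effect.

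**3. GEE without the stratum.** Stratified trials were simulated and fitted with an exchangeable GEE with sandwich standard errors. There were 3,000 runs under the null and 2,000 at an effect of 0.235. Total between-kindergarten variance stayed at ICC 0.05, and the stratum's share of it was varied. The ratio is mean reported standard error over the actual spread of the estimate.

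| Share explained | Null runs | Runs at 0.235 | Type I error, unadjusted | Type I error, adjusted |
|---|---|---|---|---|
| 0% | 0.0842/0.0831 = 1.01 | 0.0844/0.0871 = 0.97 | 4.8% | 4.7% |
| 10% | 0.0846/0.0830 = 1.02 | 0.0846/0.0819 = 1.03 | 4.6% | 5.2% |
| 25% | 0.0852/0.0818 = 1.04 | 0.0852/0.0794 = 1.07 | 4.0% | 5.8% |
| 50% | 0.0864/0.0754 = 1.15 | 0.0867/0.0740 = 1.17 | 2.8% | 6.0% |
| 80% | 0.0879/0.0687 = 1.28 | 0.0877/0.0664 = 1.32 | 1.2% | 5.6% |

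The simulated spread has a relative error of about 1/√(2 × 3000) = 1.3%, or 1.6% with 2,000 runs. This explains the scatter around 1 in the first row and much of the gap between 4% and 7% at 25%.

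**4. Second simulation, fixed steps between adjacent strata.** Scored −1, 0, 1, the strata have variance 42/62 − (24/62)² = 0.528. The stratum variance was apparently added on top of ICC 0.05.
- Step 0.2 SD: 0.04 × 0.528 = 0.021, a share of 0.021/0.071 = 30%. Reported 0.093 against true 0.087 (7 to 8% too large); type I error 3.9%.
- Step 0.3 SD: 0.09 × 0.528 = 0.0475, a share of 0.0475/0.0975 = 49%. Reported 0.105 against 0.088 (19% too large); type I error 2.0%.

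The two simulations agree once put on the same scale.

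**5. What this does to the detectable effect (80% power).** The critical value uses the reported standard error, and the remainder uses the true spread. From the null runs at a 50% share, without the stratum: 1.96 × 0.0864 + 0.84 × 0.0754 = 0.233; with it: 2.80 × 0.0751 = 0.210. At 25%: 1.96 × 0.0852 + 0.84 × 0.0818 = 0.236, against 2.80 × 0.0819 = 0.229. I prefer this to simulated power, because the same arm always received the 17/10/4 split. That shifts the unadjusted estimate slightly: (−13 + 11)/31 = −0.065 score units.

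**6. Kindergarten-level t-test (10,000 runs per scenario).** With R² the stratum's share of outcome variance, the expected ratio under exact balance is 1/√(1 − R²), or 1.05, 1.15 and 1.41 at 10%, 25% and 50%. Simulated standard errors were 4%, 13% and 34% too large, with type I error 3.9%, 2.6% and 1.0%. The simulated values fall slightly lower because 33 and 9 cannot be split evenly. Stratum-adjusted regression held type I error at 4.8 to 5.1%.

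**The case against.** **The omission is inferred.** The covariate list in section 2.7 opens with an e.g., Table 1 does not repeat even age and gender, and a condensed article may leave the full list to an analysis plan that is not shown. A reader might infer that the plan excludes the stratum; the article does not say so. This stands for the GEE models, although the list is open only within socioeconomic variables. It does not rescue the kindergarten-level tests, which Table 1(b) names and which take no stratum term in standard form.

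**The size depends on an unknown association.** The stratum counts consenting children, about 49% on average, so it is not even the kindergarten's true size. A 0.3 SD step puts the outer strata 0.6 SD apart, nearly twice the planned effect of 0.325, and raises the total ICC to about 0.0975/1.0475 = 0.09. A small association is at least as plausible. This stands, and it is why the result is a range that starts at zero.

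**The simulated outcome fits few rows of Table 1.** Most main outcomes are ordinal, nominal or dichotomous. Most secondary outcomes are differences from baseline, where stable level differences between strata cancel and size would have to predict change. This also stands: the direction carries over, but the percentages are only indicative.

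**The stratification did its job.** Its stated purpose was similar numbers of children, and 511 against 510 meets it under any model.

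**Conclusion.** The point holds conditionally. As described, the analyses do not use the stratum. If it is related to an outcome, the reported GEE standard error is too large by roughly 0 to 4% for a share of up to 25% of the between-kindergarten variance (up to 7 to 8% at 25 to 30% in the other runs), and by about 15 to 19% at half. The kindergarten-level tests are affected more. If the stratum is unrelated, nothing is lost.

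Two stronger readings are tempting and not supported. One is that standard errors will be too large as a matter of course; the article gives no link between size and any outcome. The other is that omitting the stratum forfeits the benefit of stratifying. The balance sought was achieved, and precision gained by design stays in the estimate: at a 50% share its spread is 0.0754 without stratum terms and 0.0751 with them. Only the reported standard error and the test fail to show it.

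The priority is minor, because the error is conservative and section 2.7 declares all tests explorative.

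**What to change.** State that the three-level randomisation stratum enters every GEE model, main and secondary, as a fixed covariate. For the kindergarten-level outcome, replace the named tests with stratum-adjusted regression or stratified counterparts (van Elteren for Wilcoxon, Cochran–Mantel–Haenszel for the categorical tests). If the stratum is to be left out, say so and give the reason.

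The cost is two degrees of freedom and one sentence; the stratum is known for every kindergarten. With 62 clusters the adjusted sandwich test is slightly liberal: 4.7 to 6.0% in one simulation, 5.6 to 5.9% in the other. A small-sample correction of the sandwich variance (for example Kauermann–Carroll) with a t reference distribution is therefore advisable. For dichotomous or ordinal outcomes under a logit link, the adjusted odds ratio is conditional on stratum, and the report should say so.
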